### Trial design {8}

The SWEMMA trial is designed as a randomized, controlled, open, national, multicenter superiority trial with two parallel groups and a primary endpoint of reoperation within 3 months following either procedure. Clinical secondary outcomes assessments at 3 months and 12 months will be blinded. Randomization will be performed in blocks with 1:1 allocation.

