#### Secondary outcome measures:

I.Difference in neurologic disability, assessed by modified Rankin Scale (mRS), between groups at 3 and 12 monthsII.Difference in quality of life, assessed by EuroQoL 5D (EQ-5D) between groups at 3 and 12 monthsIII.Difference in residual hematoma volume (mL) between groups, assessed by NCCT of the head at 3 months post treatmentIV.Technical success rate of endovascular treatment (percentage of interventions), defined as post procedurally no visualization of antegrade flow in branches of the MMA distal to non-target arterial branches, i.e., arteries to the orbit or cranial nerves, on final angiogramV.All complication rates; number and severity of adverse and serious adverse events between groups.VI.Composite endpoint: difference in death or reoperation frequency within 3 and 12 months after treatment between groups

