#### Sample size {14}

The study will include at least 288 patients (control + intervention), with 144 patients per arm. The required total sample size was estimated based on the expected proportion of re-operations (primary outcome) within the control and intervention arms using a two-sided likelihood ratio test with alpha = 0.05 (type I error), beta = 0.2 (type II error), and power of 80% (1-beta). The null hypothesis for this study is that there is no difference between embolization versus surgery for cSDH. The alternative hypothesis was conservatively pre-specified as a different proportion of re-operations between the groups (i.e., a two-sided test was used for power calculation). The expected proportion in the control arm was defined as 17%. This number was based on the average excess operations per patient operated for cSDH in South of Sweden (Skåne) during the last 5 years (2016–2020), as well as a report from the Skåne University Hospital [17]. The expected proportion in the intervention arm was set to 6.5% based on previous reporting evaluating the safety and efficacy of embolization of cSDH as sole treatment [13].

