#### Secondary variable analyses

Binary secondary outcomes (i.e., technical success rate, all complications rate, and composite outcome of death and re-operation within 3 months) will be analyzed using logistic regression models (as described for the primary outcome). Kaplan–Meier time-to-event analysis with follow-up time as the time scale will also be used to assess the impact of intervention on the composite outcome of death and re-operation with differences between survival curves assessed using the likelihood ratio test. Ordinal secondary outcomes (i.e., mRS and EQ5D) will be assessed at 3 and 12 months after treatment. To assess the effect of intervention at each time point, ordinal logistic regression models will be used. For the continuous secondary outcome (i.e., hematoma volume), a generalized linear model will be used. All analyses will account for enrolment center and baseline characteristics unevenly distributed between study arms when applicable.

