## Discussion

The hypothesis of this trial is that endovascular treatment alone is safe and effective with a reduced reoperation rate compared to surgical evacuation in cSDH patients with clinical indication for surgical treatment.

The rationale for the trial design is the encouraging results with reduced reoperation rate for patients treated by endovascular embolization alone, where the reoperation rates are similar to those seen for endovascular treatment adjuvant to surgical evacuation. However, when routinely using endovascular treatment as an adjunctive, the increased complication rate by having two separate procedures may potentially outweigh any benefit of the combined treatments.

A minimally invasive treatment with reduced recurrence risk and comparable complication rates has however the potential for paradigm shift in the treatment of cSDH. Not within the scope of this trial, but eMMA has also been associated with a reduction in healthcare costs, the primary driver being fewer treatments needed [20]. A drawback of the endovascular treatment is that resolution of the hematoma is slower than prompt neurosurgical evacuation. Limited data on timing of clinical improvement with upfront eMMA is currently available. In our experience, a delay of clinical and radiological improvement of 5–10 days and 4–6 weeks respectively can be expected.

Internationally, treatment strategies for bilateral cSDH varies significantly, and reoperation rates for this group seem to be somewhat higher than unilateral cSDH, either by ipsilateral recurrence or opportunistic expansion of the unoperated side [21]. For bilateral cSDH randomized to neurosurgery and unilaterally evacuated at index procedure, additional analysis including subsequent operative treatment on the contralateral side will be performed.

When designing this trial, we have striven to follow clinical routine care as much as possible to facilitate transferal into clinical routine care, should the results be positive.

The trial is academically driven and locally funded by the collaborating efforts of the Neurosurgery and Interventional Neuroradiology departments at Skåne University Hospital. Sponsor is Region Skåne, the publicly funded healthcare provider for the south region of Sweden.

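### The all-complications comparison contains the primary outcome, so fewer reoperations alone would make embolization look safer

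*Protocol article*

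**What the plan says.** Under Secondary outcome measures, outcome V is "All complication rates; number and severity of adverse and serious adverse events between groups". No event type is excluded and no causal relation is required. Secondary variable analyses lists the "all complications rate" among the binary outcomes, to be modelled by logistic regression as for the primary outcome. The section on adjustment of significance levels sets p < 0.01 for secondary outcomes.

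Adverse event classification and definitions treats a pre-existing disease as an adverse event if it comes back after recovery or gets worse during the study. An adverse event is serious if, among other criteria, it leads to hospital admission or a longer stay. The only exemption is for planned admission for a pre-existing condition or a procedure that the protocol requires, and then only without serious deterioration.

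Event reporting requirements is worded more narrowly. Conditions present before the procedure are not reported, and worsening is reported where a trial procedure caused it.

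Outcomes {12} makes reoperation for the hematoma on a treated side the primary outcome at 3 months. The sections on adverse event assessment have each event classified as procedure-related, device-related or unknown, but outcome V does not use that classification.

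**The concern.** The Discussion describes the hoped-for result as "A minimally invasive treatment with reduced recurrence risk and comparable complication rates". Those are two properties, and a reader will expect two separate pieces of evidence. As outcome V is written, the second partly restates the first. An unplanned reoperation for recurrence is neither a planned admission nor a protocol-required procedure, and the control procedure as described leaves a drain in place for 24 hours, so a surgical reoperation entails a hospital stay.

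Two consequences follow. If embolization lowers reoperation, the pooled complication rate will favour it even when the two procedures are equally safe in every other respect. Conversely, if embolization causes more procedural harm, fewer recurrences can cancel that harm in the pooled rate, and the complication rates will look comparable when they are not.

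**Working it through.** **Inputs**

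- Reoperation within 3 months, from Sample size {14}: "The expected proportion in the control arm was defined as 17" percent, and "The expected proportion in the intervention arm was set to 6.5" percent. Write p = 0.17 (control) and p = 0.065 (embolization).
- Size: 288 patients "with 144 patients per arm", allocated 1:1.
- Threshold for outcome V: p < 0.01, two-sided.
- Rate c of patients with at least one other complication: **assumption**, as the protocol gives no figure. It is taken as equal in both arms and independent of reoperation, over a range of 5% to 50%.
- Every reoperation is taken to be recorded as an adverse event: **assumption**, following the broad definition.

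**Step 1. Reproduce the plan's figure.** The unpooled formula gives n = (1.960 + 0.842)² × (0.17 × 0.83 + 0.065 × 0.935) / 0.105² = 7.849 × 0.2019 / 0.011025 ≈ 143.7, so 144 per arm. The likelihood ratio test that the protocol names also gives 144 per arm (power 80.3%). The plan's figure is reproduced.

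**Step 2. Patients carried into outcome V.** Expected patients with a reoperation: 144 × 0.17 = 24.5 in the control arm and 144 × 0.065 = 9.4 in the embolization arm.

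**Step 3. All-complications rate with equal procedural safety.** The rate per arm is q = 1 − (1 − c)(1 − p), and the gap between arms is (1 − c) × 10.5 points. For c = 10%: 1 − 0.90 × 0.83 = 25.3% v 1 − 0.90 × 0.935 = 15.9%. The last column is the power of a two-proportion test at 144 per arm and alpha 0.01. Exact enumeration of the likelihood ratio test agrees within about one point.

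| c (assumed) | Control | Embolization | Gap (points) | Odds ratio | Chance of p < 0.01 |
|---|---|---|---|---|---|
| 5% | 21.2% | 11.2% | 9.98 | 0.47 | 39% |
| 10% | 25.3% | 15.9% | 9.45 | 0.56 | 28% |
| 20% | 33.6% | 25.2% | 8.40 | 0.67 | 16% |
| 30% | 41.9% | 34.6% | 7.35 | 0.73 | 10% |
| 50% | 58.5% | 53.3% | 5.25 | 0.81 | 5% |

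With reoperation left out, both arms have rate c, the odds ratio is 1.00, and the chance of p < 0.01 in either direction is about 1% (exact 1.0% to 1.2% over this range).

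**Step 4. How much excess harm the pooled rate could absorb.** The totals are equal when the embolization arm's rate of other complications is 1 − (1 − c) × 0.83 / 0.935, where c is now the control arm's rate.

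- c = 5%: 1 − 0.7885 / 0.935 = 15.7%
- c = 10%: 1 − 0.747 / 0.935 = 20.1%
- c = 20%: 1 − 0.664 / 0.935 = 29.0%
- c = 50%: 1 − 0.415 / 0.935 = 55.6%

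**Step 5. Set the two reporting rules side by side.** The definitions section makes recurrence after recovery, or worsening, an adverse event whatever its cause. The reporting section asks for worsening to be reported when a trial procedure caused it. A hematoma that re-accumulates through the natural course of the disease is an adverse event under the first and may not be reportable under the second. Steps 2 to 4 follow the first rule. If sites follow the second, some recurrences drop out of outcome V, and the number may differ between sites.

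**The case against.** A reader might infer that outcome V simply repeats the primary outcome. It does not. V covers every adverse event, related or not, from consent to study exit, in patients aged up to 90. The carry-over shrinks by the factor (1 − c), and where background events are common it is modest: at c = 50% the chance of a significant result is 5%, against about 1% without reoperation. It may be larger for serious events alone if those are less frequent.

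A second operation is a real harm to the patient, so counting it in an all-inclusive rate is legitimate. That stands, and it is why the all-inclusive rate should stay. The overlap with composite outcome VI is no fault either, since VI is openly defined as death or reoperation.

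The premise is also not beyond dispute. The narrower reporting rule could keep some recurrences out, and a hematoma that merely persists after embolization has not recurred after recovery, though it may count as worsening. That limits how many reoperations enter V, but it leaves the protocol giving two answers on what is recorded.

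Finally, relatedness is recorded for each event, and the Data Safety Monitoring Board adjudicates every serious event on the same scale, so procedural harm can be separated from the data collected. That also stands. But the stated outcome and its analysis do not use relatedness, and the primary safety endpoint mentioned in the Data Safety Monitoring Board section is not defined among the outcomes. How endpoint events are tabulated could be settled in an analysis plan. The point here is different: the outcome, the definitions and the model that the article does state together place the primary event inside the safety comparison.

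**Conclusion.** The point holds in limited form. Outcome V contains the primary outcome, and at the design reoperation rates this alone moves the all-complications rate in favour of embolization by about 5 to 10 points as the assumed rate of other complications runs from 50% down to 5%. The pooled rate could absorb a rise in embolization's other complications from 10% to 20.1%, or from 5% to 15.7%.

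This rests on four assumptions: embolization lowers reoperation as the trial expects, every reoperation is recorded as an adverse event, other complications are independent of reoperation, and (for the rates in Step 3) they are equally frequent in both arms. The reoperation rates are 3-month figures, whereas adverse events are collected until study exit.

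A reader might go further and infer that the trial cannot assess procedural safety, or that its safety comparison is invalid. The documents do not support that: relatedness is collected, an all-inclusive harms rate is a proper outcome, and no formal test of comparable complications is planned. The sample size is unaffected. This is a cheap improvement to what the trial can conclude about safety, together with one inconsistency between two sections that must be resolved.

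**What to change.** - Keep the all-inclusive rate. Pre-specify beside it outcome V without recurrence or progression of the hematoma and without the reoperation itself. Complications arising from a reoperation still count.
- Use the relatedness classification already recorded to show procedure-related and device-related events by arm.
- Reconcile Adverse event classification and definitions with Event reporting requirements on whether a recurrence is recorded as an adverse event, so that all sites record the same thing.
- Make these changes before any comparative results are seen.

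The cost is one flag in the case report form and one extra table row. The downside is that the report carries two safety rates instead of one and must explain the difference. Sample size and patient care do not change.

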#### Participant timeline {13}

**Table Tabb:** 

**Visit nr:**	1	-	2	-
**Week/month nr:**	Week 1	Week 2	Month 3 (2–4)	Month 12 (10–14)
Medical history	X			
Physical examination	X			
Inclusion/exclusion criteria	X			
Informed consent	X			
Randomization	X			
Treatment	X			
Medical record review	X		X	
Head NCCT	X		X	
Follow-up telephone interview		X	X	X
National registry data reviews			X	X

#### Sample size {14}

The study will include at least 288 patients (control + intervention), with 144 patients per arm. The required total sample size was estimated based on the expected proportion of re-operations (primary outcome) within the control and intervention arms using a two-sided likelihood ratio test with alpha = 0.05 (type I error), beta = 0.2 (type II error), and power of 80% (1-beta). The null hypothesis for this study is that there is no difference between embolization versus surgery for cSDH. The alternative hypothesis was conservatively pre-specified as a different proportion of re-operations between the groups (i.e., a two-sided test was used for power calculation). The expected proportion in the control arm was defined as 17%. This number was based on the average excess operations per patient operated for cSDH in South of Sweden (Skåne) during the last 5 years (2016–2020), as well as a report from the Skåne University Hospital [17]. The expected proportion in the intervention arm was set to 6.5% based on previous reporting evaluating the safety and efficacy of embolization of cSDH as sole treatment [13].

#### Recruitment {15}

Potential candidates for inclusion are screened daily at the department of neurosurgery by a research nurse in close conjunction with physicians on call. Eligible patients will be offered participation in the trial. Extrapolating from previous reporting [17], approximately 50% could potentially be included in the trial, based on clinical parameters only (GCS, Markwalder). Applying all inclusion and exclusion criteria, the inclusion ratio could be slightly lower.

### Assignment of interventions: allocation

#### Sequence generation {16a}

Treatment assignment will be performed by a computer-generated randomization schedule, using permuted blocks of random sizes. To ensure concealment, block sizes will not be disclosed.

#### Concealment mechanism {16b}

Participants will be randomized using a web-based randomization tool within the RedCap system, also to be used for data collection (eCRF). Allocation will not be disclosed until the participant has been recruited and baseline data entered.

#### Implementation {16c}

RedCap, including allocation sequence generator, will be provided and administered by the independent monitor organization Forum Söder. Enrolment will be performed by an attending physician or trial staff physician responsible for recruitment. Patients fulfilling all inclusion criteria and none of the exclusion criteria will be randomized. After the enrolling physician has registered all necessary baseline data in RedCap, the system will disclose treatment arm allocation and assign a unique study enrolment number to the subject.

### Assignment of interventions: blinding

#### Who will be blinded {17a}

Treatment allocation is not blinded. Assessments at 3 months and 12 months of clinical outcomes will be conducted via telephone by an assessor blinded to treatment allocation. Subject will at initiation of interview be urged not to disclose received treatment.

#### Procedure for unblinding if needed {17b}

Given the nature of the trial, no specified circumstances for unblinding are relevant.

### Data collection and management

#### Plans for assessment and collection of outcomes {18a}

##### Primary outcome

The diagnosis of cSDH will be made on current imaging and clinical status of the included subject at the time of admittance to the recruiting neurosurgery department. Relevant clinical, radiological, and procedural data will be manually transferred from the participant medical records to the electronic case report form (eCRF). Data on reoperation (Swedish National Board of Health and Welfare Statistics Database) and date of death and primary cause of death (National Cause of Death Registry) will be collected at 3 months and 1 year post procedure. This data will be transferred to the eCRF. Participant medical records will be used to double-check the validity of the register data.

##### Secondary outcomes

Clinical outcomes: Structured telephone interview with the trial participant will be undertaken at 3 months (2–4 months) and 12 months (10–14 months). Neurological disability will be assessed using the modified Rankin Scale (mRS). mRS is a 6-point grading scale frequently used worldwide in assessing neurologic functionality in stroke and other CNS pathology patients [18]. 0 = no symptoms and 6 = death. Validated questionnaires of mRS are available in Swedish.Quality of Life will be measured using the EuroQoL 5D grading scale (EQ-5D). The EQ-5D is a standardized questionnaire used to measure quality of life in five dimensions—mobility, self-care, usual activities, pain and discomfort, anxiety and depression) and a rating of overall health using a visual analog scale (VAS) [19]. Validated questionnaires in Swedish are available and will be mailed to the participant a week before telephone interview.Change in hematoma volume at 3 months: Routine head NCCT performed at radiology department most conveniently located for the trial participant. Imagery requested and (if applicable) electronically transferred to the research institution through existing secure and firewall protected clinical PACS systems. Relevant measurements processed with automated computer software within the Sectra IDS7 PACS and/or dedicated hematoma measurement software within the Sectra platform (Qure.ai).Technical success: endovascular treatment imagery and associated procedure description or index operational procedure description requested from treating hospital and electronically transferred to research institution. Review of participant eCRF.Safety/adverse events/complications: Subjects’ medical records requested from treating hospital and local hospital and data manually transferred to the eCRF. Neuroendovascular treatment imagery (if applicable) and participant eCRF reviewed.Composite death or reoperation within 3 and 12 months; data from the Swedish National Board of Health and Welfare Statistics Database (reoperation) and National Cause of Death Registry (date of death, primary cause of death) will be collected at 3 months (2–4 months) and 1 year (10–14 months) post procedure.

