#### Outcomes {12}

Primary outcome measure:

The primary outcome is the difference in reoperation frequency within 3 months between the two groups. Reoperation is defined as any operative (surgical or endovascular) treatment regarding cSDH on the previously treated side(s).

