#### Event reporting requirements

Any adverse event that occurs during the study must be recorded and reported using the appropriate adverse event eCRF and recorded in the subject’s medical records.

These will include events occurring from the point of consent until a subject exits the study. The investigator must sign each AE eCRF report. Investigators must obtain all information available to determine the causality and outcome of the AE and to assess whether it meets the criteria for classification as serious and the relationship of each adverse event to the procedure or device. This determines whether it requires notification to the sponsor, regulatory agency, and, as applicable, EC, within the specified reporting timeframe. AEs will be categorized using the definitions in Sects. 18.1–18.5.

Pre-existing medical conditions or symptoms occurring prior to the start of the procedure should not be reported as adverse events. In the situation where there is a worsening of a pre-existing medical condition or symptom due to a study related procedure, an adverse event should be reported.

In the case of any AE, the investigator shall submit to Sponsor a report within 10 working days after the investigator first learns of the event.

The investigator is required to report all SAEs within 24 h after first learning of the event to the sponsor. The primary method of reporting SAEs will be through the eCRFs. If the database is unavailable, the investigator may fax or email in the information. As soon as the database becomes available, the investigator must complete data entry. Depending upon the nature and seriousness of the adverse event, the sponsor may request the investigator to provide anonymous copies of the subject’s available supporting documentation (such as the subject’s laboratory tests, hospital records, discharge reports, autopsy reports, investigator summaries, etc.) to document the adverse event. The sponsor is responsible in Europe for ensuring that the required and adequate information concerning the reported SAE is relayed to the appropriate Ethics Committee and Competent Authority using the MEDDEV 2.7/3 SAE Report Table. All other adverse events (i.e., other than serious adverse events) must be recorded on the appropriate adverse event eCRF.

The sponsor, in cooperation with the Investigator, will assess all serious adverse events for potentially reporting to the Regulatory Authorities and EC.

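### Registry reads for the 3- and 12-month event outcomes may take place before the horizon has passed; the 12-month composite can be truncated, and the month-12 record check is not scheduled

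*Protocol article*

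**What the plan says.** **Horizons.** Under Outcomes {12}: "The primary outcome is the difference in reoperation frequency within 3 months between the two groups". Under Secondary outcome measures: "Composite endpoint: difference in death or reoperation frequency within 3 and 12 months after treatment between groups".

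**When the data are read.** In section {18a}, the Primary outcome text says that reoperation and death data "will be collected at 3 months and 1 year post procedure", with no window. The Secondary outcomes text says that the same registry data for the composite "will be collected at 3 months (2–4 months) and 1 year (10–14 months) post procedure". The Participant timeline {13} puts the row "National registry data reviews" in the columns for month 3 (2–4) and month 12 (10–14).

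**Record check.** The Primary outcome text adds: "Participant medical records will be used to double-check the validity of the register data". In the timeline, the row "Medical record review" is marked at week 1 and month 3 only.

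**Analysis.** The 3-month reoperation proportion is compared by logistic regression, with Kaplan–Meier analysis alongside. The composite within 3 months is also analysed by logistic regression, and Kaplan–Meier is planned for the composite as well.

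**Adverse events.** Under Event reporting requirements: "These will include events occurring from the point of consent until a subject exits the study".

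**The concern.** A window of plus or minus one or two months suits a score taken by telephone, because the score describes the patient on the day of the call. It does not suit a count of events up to a fixed date. If the register is read before that date, the remaining time is unobserved, and a binary outcome records the participant as event-free unless someone looks again.

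The article does not require extraction to follow the horizon, and it does not say that a later read revises an earlier status. A site can therefore follow the schedule exactly and still return an incomplete count. At stake are completeness of the 12-month composite, some power for the primary outcome, and the check of 1-year register data against records.

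**Working it through.** **1. Windows against horizons**

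| Outcome | Horizon | Earliest permitted read | Unobserved at earliest read | Later read planned? |
|---|---|---|---|---|
| Reoperation (primary); composite at 3 months | 3 months | month 2 | 1 of 3 months | yes, months 10–14 |
| Composite at 12 months | 12 months | month 10 | 2 of 12 months (17%) | no |

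The last column separates the two cases. The first gap can be closed from data that the plan already collects. The second cannot be closed by any scheduled registry read. If 12-month reads were spread evenly over months 10–14 (an assumption), half would fall before month 12, short by 1 month on average, so the mean shortfall would be 0.5 × 1 = 0.5 of 12 months. The article gives no 12-month event rate, so this cannot be turned into a number of events.

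**2. The plan's own sample size**

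Inputs from Sample size {14}: 17% versus 6.5%, two-sided alpha 0.05, power 80%, likelihood ratio test, 144 per arm.

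n per arm = (1.960 + 0.842)² / {2[KL(p₁, p̄) + KL(p₂, p̄)]}, where p̄ = 0.1175 and KL(p, q) = p ln(p/q) + (1−p) ln[(1−p)/(1−q)].

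- KL(0.17, 0.1175) = 0.01188 and KL(0.065, 0.1175) = 0.01555.
- n = 7.849 / (2 × 0.02743) = 143.06, so 144 per arm and 288 in total. The stated figure is reproduced.

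The pooled normal formula gives a power of 79.3% at 144 per arm: (0.105 × √144 − 1.960 × 0.4554) / 0.4493 = 0.818, and Φ(0.818) = 0.793. This is the baseline for step 3.

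**3. Primary outcome if early reads are never updated**

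The article gives no timing of reoperations, so a constant hazard over 3 months is assumed. The proportion seen by month t is 1 − (1 − p)^(t/3). Events after month 3 are not counted.

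| Read time | Control | Embolization | Power at 144 per arm |
|---|---|---|---|
| Month 3 or later | 17.0% | 6.5% | 79.3% |
| Spread evenly over months 2–4 | 15.7% | 6.0% | 75.8% |
| All at month 2.5 | 14.4% | 5.4% | 72.0% |
| All at month 2 (extreme) | 11.7% | 4.4% | 62.6% |

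Expected events with full follow-up are 144 × 0.17 + 144 × 0.065 = 24.5 + 9.4 = 33.8. With evenly spread reads they are 144 × 0.1568 + 144 × 0.0597 = 22.6 + 8.6 = 31.2, a loss of about 2.7 (1.9 control, 0.8 embolization).

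If reoperations cluster early, the loss is smaller: with 95% of events captured, power is 76.9%; with 90%, 74.4%. If the 10–14 month read updates the 3-month status by operation date, the loss is zero.

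**4. The record check at 1 year**

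The Primary outcome text collects register data at 3 months and 1 year and then says, without limiting it to one time point, that records will be used to verify them. The timeline schedules a record review at month 3 but not at month 12. The two passages do not agree for the 1-year data.

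**The case against.** The strongest reply is that a collection window is not an ascertainment window.

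- **Late reads do no harm.** A reader might infer that operations after 3 months would be counted when the read falls at month 4. The outcome definition already limits events to 3 months, and Kaplan–Meier analysis needs operation dates, so later events can be cut off by date. This part of the objection stands.
- **The primary outcome has other protection.** Its own data-collection text carries no window; the 2–4 months reach it only through the timeline. The 10–14 month read covers the first 3 months for everyone still followed. Adverse events are recorded until study exit, and serious ones, which include in-patient hospitalization, are reported within 24 hours. An early miss is therefore recoverable. What remains is that the article does not say the 3-month status will be updated.
- **Kaplan–Meier can censor.** This is true if follow-up is censored at the read date. It does not rescue the composite as defined, which is a frequency within 12 months. Adverse event capture may not help either: if a participant leaves the study at a final contact in month 10, that source stops too.
- **Loss by arm.** A reader might infer that failures are missed more often after embolization because the hematoma resolves more slowly. Both arms have the same windows, and the 4–6 weeks in the Discussion is a delay to radiological improvement, which ends before month 2. Nothing in the article shows unequal loss.
- **Complications at month 12.** A reader might infer that they have no source. They do: ongoing adverse event recording, and records requested from the treating and local hospitals. The blank timeline cell removes a scheduled validity check, not the data.
- **Level of detail.** Extraction rules are often left to an analysis or data-management plan. Here, however, the article states a rule, and that rule permits reading before the horizon.

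**Conclusion.** The point holds in limited form. For the 12-month composite, the stated schedule can leave up to 2 of 12 months unobserved with no later read. This follows from the text alone, although its effect on event numbers cannot be computed from the article.

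For the primary outcome the loss is conditional. It needs reads before month 3 and no later update. Under those conditions and a constant hazard, power falls from about 79% to about 76% with evenly spread reads; the 63% figure needs every read at month 2 and marks only the extreme. With updating, nothing is lost. The documents do not support a claim that primary follow-up is certainly truncated, or that it differs between arms.

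The missing month-12 record review is a separate, smaller inconsistency between the timeline and the data-collection text.

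**What to change.** 1. State that registry and record data are extracted no earlier than 3 months and 12 months after the procedure for every participant.
2. Classify each event by its date of operation or death against those fixed cut-offs, whenever the extraction takes place.
3. Keep the 2–4 and 10–14 month windows for the telephone scores, and the 2–4 month window for the head CT.
4. Reconcile the timeline with the Primary outcome text of section {18a}, either by marking a medical record review at month 12 or by stating that the check applies to the 3-month register data only. The first is preferable, because reoperation counts only on the previously treated side and a record check can confirm the side.

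A sensitivity analysis running past month 3, to pick up operations prompted by a late scan, would be optional; the fault described here does not require it.

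The cost is slightly later extraction and, if the month-12 review is added, one more record check per participant by existing staff. The sample size of 288 stands.
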